#### Secondary clinical outcome

The secondary aims are to evaluate the effect of EPIC Wheels on wheelchair skill safety, wheelchair use confidence, satisfaction with activity performance, mobility, divided-attention, and health-related quality of life.

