### Sample size

To address the feasibility indicators, the number of subjects is large enough to represent the target population and assess the feasibility criteria [36]. In addition, the sample size is powered to detect a statistically significant difference between groups and provide a reasonable estimate of a treatment effect. With a 2 × 2 factorial design, sample size can be calculating using each main factor independently, and then determined by selecting the larger of the two estimates [37]. Our calculations are based on the primary clinical outcome measure (the Wheelchair Skills Test version 4.1, WST), as this will be used in subsequent EPIC Wheels studies. Research in the field of wheelchair skills training is still maturing, with three published studies using actual users, and given the novel home program approach an α of 0.10 was selected to ensure a potentially beneficial treatment effect would not go undetected (Type I error rate). Given the absence of data regarding the impact of extra wheeling, we opted to use a comparable effect size (*f* = 0.54) in the second factor calculation. To minimize the risk of identifying such an effect merely by chance (Type II error), the study is powered at 90%. Based on a sample size calculation for analysis of covariance (ANCOVA) each of the four groups would require eight subjects for a total of 32 participants. In previous Canadian trials, a 9 to 18% dropout rate has been reported; conservatively adjusting for a 25% dropout rate (32/0.75), a total study *N* of 44 is planned (*n* = 11 for each group).

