Previously published studies have used younger or mixed age populations; data specific to older adults are not available. We obtained permission to use a data subset (adults >50 years) from a yet-to-be published study ([name], personal communication) that provided WST change scores following training and powered our study to capture a comparable change (*m* = 9.3%; *s* = 9.5%). A difference of 9.3% corresponds to an acquisition of three additional skills on the WST; previous studies report that subjects perceive a clinically important difference with such improvements [17,18]. In fact, the skills performed on the WST are sequenced from simple (for example, rolling forwards) to moderate (for example, propelling on carpet) to complex (for example, ascending a 10° ramp). Research literature reporting on MWC use among older adults specifically implicates carpet, inclines, curbs, gravel, and poor sidewalk conditions as barriers to independent mobility [7]. Acquisition of even one of these important skills could quite reasonably represent a minimally clinically important difference (MCID) to wheelchair users, their caregivers, and those providing training. No formal MCID has been established for the WST; however, using data from a Canadian trial [18], a smallest detectable difference calculation suggests that a difference of 9.2% would exceed any measurement error or noise [38]. A reliability change index calculation indicates that 3.0% is the minimal detectable change required and is a reasonable proxy for MCID [38].

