The clinical outcome measures are collected at baseline (pre-randomization) and post-treatment (1 month). The primary outcome is wheelchair skill capacity, measured using the Wheelchair Skills Test 4.1 (WST) [14]. The WST is a structured assessment with 32 discrete mobility skills required to perform social roles in the community, each scored dichotomously as pass or fail, producing a total skill capacity score (0 to 100%) with a higher score reflecting more skills acquired. The WST is sufficiently sensitive to detect proximal effects of training; can be completed in approximately 30 minutes; and does not demonstrate floor or ceiling effects [16]. Two systematic reviews of available wheelchair skill outcome measures confirmed that the WST has the strongest psychometric properties and has been used most extensively in clinical trials [49,50]. The WST has demonstrated reliability for test-retest (intraclass correlation coefficient (ICC) = 0.90), intra-rater (ICC = 0.96), and inter-rater (ICC = 0.97) administration [16]. Construct validity has been supported by significant relationships with predictive variables of age, sex, MWC experience, diagnosis, and use of a lightweight wheelchair, which together accounted for 35% of variability in WST score using multiple regression (adjusted *R*^2^ = 0.35) [16]. Concurrent validity has been established through positive correlation with two criterion measures: therapists’ global assessment of user ability (*R*_S_ = 0.39 - 0.40) and the Functional Independence Measure (admission score *R*_S_ = 0.38; discharge score *R*_S_ = 0.31) [16,51].

Secondary clinical outcomes reflect more distal impacts of the intervention. Given the dearth of evidence in the literature, there is substantial value in understanding the relationship between skill acquisition and safety, confidence, community participation, mobility, and utility. Seven secondary measures contribute to discerning a clinically important impact of the EPIC Wheels intervention.

• WST 4.1 skill safety. The WST also provides a total skill safety score (0-100%) reflecting the number of skills addressed in a safe manner (higher score indicates greater safety), regardless of whether the skill is acquired or not. This is of considerable importance, since training also involves learning to recognize risks and limitations.

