ANCOVA will be used to compare post-treatment scores between groups for WST skill safety, wheelchair confidence (WheelCon), safety risk (WheelTalk), and mobility (LSA) as a secondary analysis. In each case, baseline score will be used as a covariate. Subjects’ satisfaction with performance of meaningful activities (WhOM score) will be analyzed using analysis of variance (ANOVA). Mean administration time for the HUI3 will be calculated and a preliminary evaluation of change in the treatment group will be conducted. Endpoints and change analyses will also be conducted to compare their precisions with ANCOVA. Summary and descriptive statistics for distance and speed (mean and standard deviation) and bouts of activity (counts) will be calculated for the data logger data.

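### WhOM is given ANOVA with no baseline covariate, and HUI3 has no planned between-group estimate, although the aim is an effect of EPIC Wheels on both

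*Protocol article*

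**What the plan says.** The Secondary clinical outcome section of the protocol article sets out to "evaluate the effect of EPIC Wheels on wheelchair skill safety, wheelchair use confidence, satisfaction with activity performance, mobility, divided-attention, and health-related quality of life". Satisfaction is measured by WhOM and health-related quality of life by HUI3. The Data collection section states: "The clinical outcome measures are collected at baseline (pre-randomization) and post-treatment (1 month"). It makes no exception for WhOM or HUI3.

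The Statistical analyses section then treats the secondary scores in three ways:

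- WST safety, WheelCon, WheelTalk and LSA: between-group ANCOVA, each with its own baseline as covariate.
- Satisfaction: "WhOM score) will be analyzed using analysis of variance (ANOVA"). No covariate, response variable or reason is given.
- HUI3: mean administration time, and "a preliminary evaluation of change in the treatment group will be conducted".

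Four other statements bear on the point. The same section opens by planning descriptive summaries of the outcome variables by group. It argues that ANCOVA should be the most powerful analysis because preliminary WST data suggest a pre-post correlation of about 0.5. After the HUI3 sentence it adds endpoint and change analyses, to compare their precision with that of ANCOVA. The HUI3 entry under Data collection gives that measure a narrower purpose: whether cost-utility data can feasibly be collected, and what changes might be expected. The Feasibility indicators section likewise lists a health utility index as a resource issue.

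**The concern.** WhOM and HUI3 appear in the same list of effect aims as the other secondary outcomes, yet neither gets the analysis that the article itself argues is best.

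For WhOM the stake is precision. A baseline satisfaction score should be on file for each participant, and the plan as written does not use it as a covariate.

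For HUI3 the stake is whether the aim can be answered. Change in the EPIC arm alone combines the programme with anything else that moves over a month: time, trainer attention, use of a tablet and repeat questioning. The control arm was built with matched sessions and an identical tablet to separate some of these from the programme. Participants have used a wheelchair for under a year, so some change without training is plausible. The EPIC arm also pools participants with and without extra wheeling. A one-arm change would be a weak guide to the between-group difference in the larger trial, which the Discussion says will address cost-effectiveness.

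**Working it through.** **Inputs.** From the Sample size section: "an α of 0.10 was selected to ensure a potentially beneficial treatment effect would not go undetected"; "the study is powered at 90" per cent; "we opted to use a comparable effect size (*f* = 0.54) in the second factor calculation"; 32 evaluable participants, 8 per cell. With 1:1:1:1 allocation each main effect compares 16 with 16. From Statistical analyses: pre-post correlation ρ of about 0.5 for the WST. No ρ is given for WhOM or HUI3, so 0.5 is an assumption there and a range is shown. Equal variances at the two visits are assumed.

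**The plan's own figures.** Noncentral F with 1 numerator df, four groups, one covariate and λ = f²N, at f = 0.54 and α = 0.10, gives a minimum N of 31. Rounding up to four equal cells gives 32, where power is 90.9%. The stated 32 reproduces. The ratio of ANCOVA to change-score variance is (1 + ρ)/2, which is 0.60 at ρ = 0.2 and 0.90 at ρ = 0.8. That reproduces the article's stated saving of 10 to 40%.

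**WhOM.** Error variance relative to a post-score ANOVA is 1 for that ANOVA, 2(1 − ρ) for change scores and 1 − ρ² for ANCOVA. The excess of change score over ANCOVA is 2/(1 + ρ) − 1.

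| ρ | Post-score ANOVA | Change-score ANOVA | ANCOVA | ANCOVA saving v post-score | Change-score excess over ANCOVA |
|---|---|---|---|---|---|
| 0.3 | 1 | 1.40 | 0.91 | 9% | 54% |
| 0.5 | 1 | 1.00 | 0.75 | 25% | 33% |
| 0.7 | 1 | 0.60 | 0.51 | 49% | 18% |

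To put this in power terms, take an effect for which ANCOVA has the plan's 90.9% at N = 32, that is f = 0.54 on the residual scale. A post-score ANOVA then works with f = 0.54 × √(1 − ρ²), which is 0.468 at ρ = 0.5. Its power is 82.5% (88.4% at 0.3, 68.6% at 0.7). It needs N = 41 for 90% (34 at 0.3, 60 at 0.7), against 31 for ANCOVA. The effect size is borrowed from the WST, so the power figures are illustrative. The variance ratios do not depend on it.

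**HUI3.** In units of the HUI3 SD, at ρ = 0.5:

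- EPIC-minus-control ANCOVA, 16 v 16: SE = √(0.75 × 2/16) = 0.31.
- EPIC-arm change only, n = 16: SE = √(2 × 0.5/16) = 0.25.

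The second is smaller but belongs to a different quantity. Its expectation is the treatment effect plus the change that would have occurred under control. More participants shrink the SE and leave that second term in place.

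**The case against.** **WhOM.** The article does not say that baseline is left out. An ANOVA on change scores or with repeated measures fits the words, and the exact model may be in an analysis plan that is not shown. This stands, so the post-score reading is likely from the contrast with the ANCOVA sentence, but it is not literal. It does not remove the point, because a change-score ANOVA also falls short of ANCOVA. The article also does not say whether the same self-chosen activities are rated at both visits. If they are not, ρ and the gain would be lower.

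A reader might infer that the WhOM comparison is biased. It is not: randomisation keeps it valid, and the loss is in precision. A reader might also take the WhOM test-retest ICC of 0.77 as ρ and claim a 59% variance saving (1 − 0.77² = 0.41). The documents do not support that, since test-retest reliability is not a correlation across a month of intervention. Nor do they give a WhOM baseline SD from which to argue that starting levels vary widely.

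**HUI3.** The article gives this measure a limited feasibility role, and administration time plus a preliminary look at change suits that role. This is the best defence, but the stated secondary aim does not carry the limit. A reader might infer that the control HUI3 data are discarded. That is too strong, because descriptive summaries by group are planned. What is absent is an inferential between-group estimate. Regression to the mean should not be cited as a demonstrated source of bias either, as eligibility sets no HUI3 threshold.

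**Endpoint and change analyses.** These are introduced as precision comparators to ANCOVA. Neither WhOM nor HUI3 has a planned ANCOVA, so the sentence does not clearly supply the missing analysis for either.

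**Conclusion.** The point holds in two parts of unequal weight.

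The HUI3 part is the firmer. The aim, the measure's stated purpose and the planned analysis do not agree, and treatment-group change cannot answer an aim framed as an effect of the programme. This rests on the text alone.

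The WhOM part is a loss of efficiency, not an error of validity. The size is about 25% of error variance at ρ = 0.5 if the ANOVA is on post-scores (9% to 49% over 0.3 to 0.7), or a variance about 33% above ANCOVA's at ρ = 0.5 if it is on change scores. Both figures rest on a correlation assumed for WhOM.

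These are secondary outcomes of a feasibility trial and the primary analysis is unaffected. The change is still worth making because it should need only data that the protocol already collects.

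**What to change.** 1. Analyse WhOM satisfaction with the same 2 × 2 ANCOVA and baseline covariate as the other secondary scores. If there is a reason for ANOVA, state it and name the response variable.
2. For HUI3, do one of two things. Either report the baseline-adjusted EPIC-minus-control difference with its confidence interval, labelled exploratory, or restate the aim in the Secondary clinical outcome section so that HUI3 is a feasibility measure only, in line with its entry under Data collection.

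The cost is wording. WhOM gives up one error degree of freedom (with four cells and 32 evaluable participants, 32 − 4 = 28 becomes 27). HUI3 gets a wider interval than one-arm change would show (SE about 0.31 SD against 0.25 SD at 16 per arm and ρ = 0.5), in exchange for an estimate of the effect named in the aim.

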## Discussion

The EPIC Wheels study is intended to establish the feasibility of a novel intervention designed to improve wheelchair skills and safety among older adult manual wheelchair users. The EPIC Wheels program is innovative in several respects. First, it offers evidence-based skills training in a home training format that has greater potential for clinical uptake. While structured training has been demonstrated to improve skill capacity, access to and related costs of one-on-one training with an expert clinician has restricted widespread adoption. Consolidating the majority of training in a home program with remote electronic monitoring by the clinician makes for a more viable option from an economic and convenience standpoint. Second, EPIC Wheels has a theory-driven design to increase effectiveness among older adults and enhance program adherence, explicitly incorporating principles of social cognitive theory (self-efficacy) and andragogy (adult learning) into the content and delivery format. In addition, older adult stakeholder groups including MWC users, their caregivers, and clinician trainers, were intimately involved during the 1-year program development process. Research related to capacity and a principled teaching method for older adults to learn wheelchair mobility skills is sparse, and this study may provide important new evidence. Third, the use of commercially available and relatively inexpensive tablet technology provides a flexible and versatile mobile training interface. Trainees can practice with the tablet on their wheelchair in their home or community environment and communicate remotely with their trainer, while clinicians can monitor training activity and communication through a web-based interface at their convenience. Finally, the factorial study design will allow broader inferences about the contributions of increased wheelchair activity and the specific attributes of the EPIC Wheels training program, as well as an interaction between these factors.

Owing to the nature of feasibility studies, several inherent limitations arise and will be addressed in the larger multi-site RCT study to follow. The potential for recruitment of novice older adult MWC users is unknown: this is an important feasibility indicator to address for future planning. Assessment of skill retention will not be addressed at this stage. Control group subjects may be more likely to drop out. Providing control group trainers with structured strategies to maintain subject enthusiasm; weekly subject contact; engaging and fun cognitive computer games, and provision of a condensed training DVD at the study conclusion will help mitigate this risk. Demonstration of a treatment effect may lack generalizability, owing to the restricted age group being targeted. Age is inversely related to motor skill acquisition, including wheelchair mobility skills. We anticipate that a training program proven to be effective with older adults should have at least as large a treatment effect in younger and stronger individuals; however, this assumption is as yet untested.

The feasibility indicators of this study will be used to construct and implement a comprehensive, multi-site RCT trial that directly measures the guiding hypotheses. This subsequent study will address skill retention using a 6-month follow-up evaluation. A large RCT will directly address evaluation of important changes in wheelchair skill and safety; wheelchair use confidence; mobility and community participation; and cost-effectiveness. Evidence for the effectiveness of EPIC Wheels would inform clinical best practice and provide justification for a pilot project where a single trainer coordinates service to a large group of wheelchair users across a broad geographical area. EPIC Wheels has great potential for use across age and diagnostic groups, including training for individuals who live in rural and remote locations where access to rehabilitation programs is not practical. EPIC Wheels provides versatility, as it can be delivered on multiple platforms including computers, tablets, smart phones, and traditional DVD. Furthermore, the inherent capacity of the tablet device (that is, GPS, accelerometers) can be incorporated into future EPIC Wheels versions to collect real-time user data on wheelchair performance; to create interactive training activities or games; to evaluate skill performance; and integration with other commercially available technology.

## Trial status

Approval has been obtained from the university Research Ethics Boards and regional health authority Research Review Committees at both sites. All study staff have been hired and trained at both sites and recruitment is currently underway.

## Abbreviations

ANCOVA: Analysis of covariance; ANOVA: Analysis of variance; EPIC Wheels: Enhancing participation in the community by improving wheelchair skills; HUI3: Health utilities index mark 3; ICC: Intraclass coefficient; LSA: Life-space assessment; MCID: Minimally clinically important difference; MWC: Manual wheelchair; RCT: Randomized controlled trial; WheelTalk: Wheeling while talking test; WhOM: Wheelchair outcome measure; WST: Wheelchair skills test, version 4.1.
